### Data analysis plan

#### Development and external validation of model

The CPRD-GOLD and CPRD-AURUM data will be cleaned and preprocessed for model development and validation, respectively. Specifically, for patient features with binary values, 0 and 1 will be mapped to the binary values. Variables with multiple categories will be split into their component categories, and each given a binary value to indicate the presence or not of the variable for each patient. Continuous variables will be kept as continuous. To reduce the high cardinality of Read codes and ICD codes, we will map both to Caliber codes,^35^ which is an expert checked mapping directory from University College London. Prodcodes can be mapped to level 2 of British National Formulary codes.^36^

A number of deep learning models will be investigated for prediction of AF in CPRD-GOLD. These will include a convolutional neural network (CNN), a recurrent neural network (RNN) and a Transformer architecture. They each possess characteristics that can capture the temporality of EHR data and the progression of a patient’s health status.

Although CNNs are typically associated with static content (eg, images and documents), they are increasingly used to uncover temporal relationships in EHR.^37–40^ The patient EHR can be converted to a temporal matrix, with one dimension corresponding to time and the other dimension corresponding to medical events (figure 1A).^37^ A one-sided convolution operation can be applied to each possible window of features in the event matrix to produce a feature map followed with max pooling (to capture the most important features) and culminating in a fully connected layer and softmax classifier. If the time dimension is embedded in 1-day increments, we have the option to learn temporal features by extending connectivity in the time dimension through a range of fusion strategies. Temporal early fusion could combine information across an entire time window to establish global patterns, temporal late fusion can be performed in the fully connected layer to model local connections and temporal slow fusion could capture both by extending the connectivity of all convolutional layers.^37^

**Figure 1 F1:**
[figure not shown]
An example of how a patient’s EHR could be represented as a temporal matrix (A) compared with a sequence (B). In (A), time is on the x dimension and medical events are on the y dimension. In (B), the temporal information, in this example, is represented as intervisit interval through timestamps (eg, t2–t1). EHR, electronic health record.

Patient EHR events including diagnoses, procedures and medications can also be represented as a sequence of codes over time, similar to words in a sentence (figure 1B). After embedding into a lower dimensional space, a one-dimensional convolutional operation over the temporal dimension with a combination of filters of different lengths could capture temporal dependencies at multiple levels.^38^

A sequence-based representation also makes patient EHR amenable to techniques that have provided breakthroughs in natural language processing, especially RNNs.^41–43^ RNNs with a gated recurrent unit model design have been successfully applied in modelling sequential structured EHR data to predict diagnoses as they can accept an input vector at each time step while storing information in a hidden layer which changes over time.^21 44–51^ We will apply the reverse time attention model (RETAIN), which has been tested for the prediction of heart failure in CPRD.^52^ RETAIN can generate temporal attention vectors at both visit and variable level by running RNNs backwards, which somewhat mimics a physician’s behaviours in examining a patient’s past visits in reverse time order and could capture the short-term time-varying events that were found to improve prediction in a previous shallow neural network model.^19 46^ Timestamps can be included to calculate the attentions for the entire visit sequence and thus provide temporal information for each visit.^46^

Finally, Transformers have become state of the art in natural language processing,^53 54^ and we will apply an adaption for EHR, BEHRT (BERT [Bidirectional Encoder Representations from Transformers] for EHR), which was originally developed in CPRD.^55^ This model’s structure, depicting each diagnosis code as a word, with each visit as a sentence and the entire medical history as a document, facilitates multihead self-attention, positional encoding and masked language model for EHR. BEHRT can define a representation incorporating information on the diseases afflicting a patient, the positional interactions of diseases and sequence of events, with the age of a patient linked to each visit to give a sense of time between diagnoses.^55^ This representation can then be used for a number of tasks including disease prediction.

Preprocessed patient-level data in CPRD-GOLD will be randomly split into an 80:20 ratio to create training and testing samples. The split ratio is not a significant factor, given the volume of the sample size. The model parameters and dropout rate will be chosen through a grid search and 10-fold cross-validation will be used (ie, 10% of the training data will be randomly selected as the cross-validation set).

While the outcome is binary, instead of just predicting 0 or 1 for a patient (new AF or not), the probability of that patient developing AF by different time points over months (1, 3, 6) and years (1, 5, 10) may be predicted. The probability of developing AF at each time point could be plotted to give an understanding of evolving risk of AF. The clinical risk prediction performance of the deep learning models will be compared against a range of classic machine learning techniques and traditional statistical predictive modelling methods including support vector machine, random forest, naïve Bayes and Cox proportional hazards model. Discrimination (Harrell’s c-statistic and AUC) and calibration metrics will be supplemented with positive and negative predictive values, precision, recall and area under precision-recall curve for all models.

The CPRD-AURUM dataset will then externally validate the model performance to assess generalisability. It has been shown that a lack of external validation has hampered the implementation of previous machine learning models in routine clinical practice.^56^

#### Identification and quantification of the magnitude of predictors

The proposed deep learning models can extract informative risk factors from EHR data. Specifically, a risk factor selection strategy proposed by Huang *et al*^57^ will be adapted to identify informative risk factors. The model will provide weights of the identified risk factors to help understand the significance of risk factors at different risk levels. The impact of the number of risk factors on AF risk prediction performance will be assessed through the curves of both AUC and prediction accuracy plotted against the number of risk factors. Some predictors, such as body mass index, blood pressure, frequency of visits and strength of the prescribed medication, may change over time. The incremental prognostic values of including these variable trajectories will be explored, and the impact on predictive accuracy will be assessed.

### Software

The deep learning model will be implemented in R (through the R studio interface) and TensorFlow or Python and PyTorch including data preprocessing, missing data imputation, model development and validation.

### Ethics and dissemination

The study has been approved by CPRD (ref no: 19_076). Those handling data have completed University of Leeds information security training. All analyses will be conducted in concordance with the CPRD study dataset agreement between the Secretary of State for Health and Social Care and the University of Leeds.

The study is informed by the Prognosis Research Strategy (PROGRESS) framework and recommendations.^58^ The subsequent research paper will be submitted for publication in a peer-reviewed journal and will be written following Transparent Reporting of a multivariable prediction model for Individual Prognosis or Diagnosis (TRIPOD) and REporting of studies Conducted using Observational Routinely collected health Data (RECORD) guidelines.^59 60^

If the model succeeds (defined as improving predicting accuracy by at least 5% compared with existing models), the algorithm could be made readily available through free-to-use software. The model will be designed to be amenable to in situ updating with new information so that prediction of an individual’s AF risk is updated contemporaneously. The algorithm could be a built-in tool for use in general practices to ‘screen’ for patients at high risk of developing new-onset AF. Future research will be needed to assess the clinical impact of this risk model. At the point when utilisation in clinical practice is possible, the applicable regulation on medicine devices will be adhered to.^61^ When in clinical use, the model itself could also be reviewed and updated by a prespecified expert consensus group on an annual basis after incorporating evidence from post-service utilisation and the curation of more data.

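### The 5% success rule does not say which architecture, horizon or dataset decides, so the verdict can be chosen after the results are seen

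*Protocol article*

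**What the plan says.** Under Ethics and dissemination the protocol article sets one threshold: "If the model succeeds (defined as improving predicting accuracy by at least 5% compared with existing models". If it is met, the algorithm may be released as free software and might be built into general practice systems.

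The Data analysis plan (Development and external validation of model) describes several candidates and several places to measure them:

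- **Architectures.** "These will include a convolutional neural network (CNN), a recurrent neural network (RNN) and a Transformer architecture". The CNN has further variants (matrix or sequence input, different fusion strategies).
- **Horizons.** "the probability of that patient developing AF by different time points over months (1, 3, 6) and years (1, 5, 10) may be predicted".
- **Datasets.** CPRD-GOLD is "randomly split into an 80:20 ratio to create training and testing samples". After that, "The CPRD-AURUM dataset will then externally validate the model performance to assess generalisability".
- **Metrics.** Harrell's c-statistic, AUC and calibration, "supplemented with positive and negative predictive values, precision, recall and area under precision-recall curve for all models". None is named as primary.
- **Comparators.** The deep learning models are "compared against a range of classic machine learning techniques and traditional statistical predictive modelling methods", whereas the success rule refers to existing models.

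The section mentions a grid search and 10-fold cross-validation for model parameters and dropout. It does not say how one architecture is chosen, and the article gives no confidence limit for the 5% gain.

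**The concern.** A rule for a single model is attached to a plan that yields many model-by-horizon-by-dataset results. As written, whoever applies it can settle after unblinding which result counts. Two analysts with identical output could reach opposite conclusions, one citing the RNN at 3 months in GOLD and the other the Transformer at 5 years in AURUM. If the most favourable result is used, the claimed gain is biased upward, most of all where events are few.

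At stake is the article's only stated success claim, which is linked to possible release for use in general practice. Data collection and sample size are not affected.

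**Working it through.** **The plan's own figures.** The success rule has no stated power, error rate or precision, so there is nothing to reproduce for it. The sample-size figure does reproduce: 200 / [(0.95 − 1) × ln(1 − 0.01/0.95)] = 377 996. It does not bear on this point.

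**Count of contrasts.** 3 architectures × 6 horizons = 18. Baseline is 1 January 2009 (Outcome ascertainment) and data end on 30 November 2018, about 9.9 years later, so 10 years cannot be fully observed. Without it, 3 × 5 = 15. Using both datasets doubles these to 30 and 36, before metrics and comparators.

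**Inputs from the documents.** About 4.5 million patients and 200 000 AF records in GOLD over the study period (Data sources and permissions), which is 20.9 years; a 20% test set, so at most about 900 000 patients.

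**Assumptions (not in the documents).** Accuracy is read as AUC; base AUC 0.80; events spread evenly over time; 5% taken as relative, 0.05 × 0.80 = 0.04; correlation r = 0.5 between model and comparator AUC; correlation 0.5 between architectures; correlation between nested horizons √(events_i / events_j); the same true gain in every contrast.

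**Precision by horizon.** Events = (200 000 / 20.9) × 0.2 × years. The Hanley–McNeil standard error at A = 0.80 uses Q1 = A/(2 − A) = 0.667 and Q2 = 2A²/(1 + A) = 0.711. With non-cases far outnumbering cases, SE ≈ √[(Q2 − A²)/events]. At 1 month this is √(0.0711/159) = 0.021. The SE of the gain is SE × √[2(1 − r)], which equals SE when r = 0.5.

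| Horizon | Test-set events | SE of gain |
|---|---|---|
| 1 month | 159 | 0.021 |
| 3 months | 478 | 0.012 |
| 6 months | 957 | 0.009 |
| 1 year | 1914 | 0.006 |
| 5 years | 9569 | 0.003 |

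The 1-month result rests on one sixtieth of the 5-year events.

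**Chance that at least one contrast shows a gain of 0.04 or more** (joint normal simulation):

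| Contrasts allowed to decide | True gain 0.02 | True gain 0.03 |
|---|---|---|
| All 15, GOLD test set | 38% | 69% |
| Without 1 month | 13% | 48% |
| 6 months and longer | 3% | 29% |
| 1 and 5 years | 0.15% | 12% |
| 5 years, three architectures | about 0% | 0.04% |
| One fixed 1-month contrast | 17% | – |
| One fixed 5-year contrast | about 0% | 0.01% |
| All 15, AURUM-sized sample (4.5 million) | 4.5% | 33% |

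**Sensitivity of the 38%.** 20% to 53% over model-comparator correlations 0.3 to 0.7 and architecture correlations 0.2 to 0.8; 16% at model-comparator correlation 0.8; 18% with the threshold at 0.05 absolute.

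**Reading the table.** One fixed 1-month contrast, with no selection, already crosses 17% of the time (0.02/0.021 ≈ 0.95 standard errors). Short-horizon imprecision therefore accounts for more of the 38% than the number of contrasts does. Choosing among three architectures at 5 years adds almost nothing by chance.

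**The case against.** The strongest reply is that the article never says the best result will be taken. It speaks of one model throughout, which fits the usual sequence of exploring candidates, selecting one in training data and validating it externally. The horizons are optional and are offered as a picture of evolving risk, not as endpoints. The success sentence is conditional, sits in the dissemination section, and is followed by statements that clinical impact needs further research and that device regulation will be followed. Detail of this kind may stand in a fuller plan.

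Much of this stands. A reader might infer that success will be declared on the maximum of 15 to 18 noisy contrasts. The documents do not support that: no such intention is stated, the contrasts are not uniformly noisy, and AURUM, sampled to match the whole of GOLD, is about five times the size of the test set. A reader might also be tempted to quote family-wise error rates. They do not apply, because the rule is a point threshold with no hypothesis test and no nominal level.

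It is also true that the undefined metric, scale and comparator can matter more. With the AUCs cited in the Introduction, a model at 0.827 has no gain over the earlier machine learning model but 0.827 − 0.725 = 0.102 over CHARGE-AF, without any noise.

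What does not stand is that this is only an omission. The article itself fixes a threshold and calls it the definition of success, yet leaves open what it is applied to. Naming the metric and comparator would still leave architecture, horizon and dataset open.

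**Conclusion.** The point holds as a defect of definition: the success rule allows the deciding architecture, horizon and dataset to be chosen after the results are known. The inflation by chance is real but local. At a true gain of half the threshold it reaches about 38% only if the 1- to 6-month horizons in the GOLD test set are eligible. It is negligible at 5 years for a gain of 0.02 or 0.03. At 1 year, and in AURUM with short horizons eligible, it becomes material only when the true gain is nearer the threshold (12% for 1 and 5 years together and 33% in AURUM, at 0.03). These figures depend on the assumed AUC reading, correlations, even event rate and equal gains. The 900 000 test set is an upper bound, so a smaller eligible cohort with the same event rate would be noisier. The finding about freedom of choice depends on none of these assumptions.

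**What to change.** Amend the success sentence under Ethics and dissemination so that it refers to one contrast:

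- **Model:** the architecture selected by cross-validation within the GOLD training data, locked before the GOLD test set and AURUM are opened.
- **Horizon:** one that follow-up supports, so not 10 years.
- **Dataset:** AURUM.
- **Measure:** one named metric, with 5% stated as absolute or relative, against one named comparator.

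Report the gain with its 95% confidence interval. Whether the lower limit must also clear 5% is the sponsor's choice, since that sets a higher bar. State in the Data analysis plan that all other architecture, horizon, metric and dataset comparisons are descriptive and cannot by themselves support the success claim.

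The cost is a few sentences, with no new data or extra model fitting. The small downside is that a gain seen only at another horizon, or with another architecture, would be reported as exploratory.

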## Introduction

Atrial fibrillation (AF) is the most common sustained cardiac arrhythmia. The current estimated prevalence is between 2% and 4%, and a 2.3-fold rise is expected due to extended longevity in the general population.^1^ While AF may present with symptomatic palpitations, for many patients, the first diagnosis of AF is only after they present with stroke or cardiac decompensation. The frequency of AF in ischaemic strokes is 20%–30%, and these are usually severe, resulting in permanent disability or fatality.^2^

Oral anticoagulants can reduce the risk of stroke by up to two-thirds in those with AF at higher risk of stroke.^3^ International guidelines recommend that patients with AF at elevated thromboembolic risk are offered stroke prophylaxis with an oral anticoagulant.^1^ Most patients with AF will have stroke risk factors, making them eligible for an oral anticoagulant. Many will have concomitant cardiovascular disease (such as hypertension, valvular heart disease or heart failure) making them eligible for further investigation or treatment. Equally, in those with AF who are at low risk of stroke (and therefore do not qualify for oral anticoagulation), surveillance for increasing stroke risk is advisable.

Thus, the early diagnosis of AF, before the manifestation of the first complication, remains a major public health challenge. Screening for AF in the community has been proposed as an approach to optimise early AF detection.^4^ Previous studies have shown that the risk of AF (often asymptomatic) increases with age.^5^ Opportunistic screening is cost-effective in patients aged 65 years or over, and among individuals aged 75–76 years old undergoing a 2-week intermittent ECG screening.^6–8^ Nevertheless, there is no current recommendation for UK population-wide systematic screening.^9^

Prediction models could contribute to AF screening by discriminating patients into risk categories, from which investigation intensity could be planned.^10^ However, models based solely on analysis of investigations may not apply in the community setting—for example, routine ECGs are not always available.^11^

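### Success is defined only as a 5% gain in predicting accuracy; read as AUC or any rank-based measure, that rule cannot see miscalibration, although the intended output is an absolute risk of AF

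*Protocol article*

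**What the plan says.** The success rule is in the Ethics and dissemination section of the protocol article: "If the model succeeds (defined as improving predicting accuracy by at least 5% compared with existing models". What follows from success is worded as a possibility: "the algorithm could be made readily available through free-to-use software". No other condition is attached.

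The Data analysis plan (Development and external validation of model) describes the output as absolute risk: "the probability of that patient developing AF by different time points over months (1, 3, 6) and years (1, 5, 10) may be predicted". It adds: "The probability of developing AF at each time point could be plotted". The same section lists the performance measures for all models: "Discrimination (Harrell’s c-statistic and AUC) and calibration metrics will be supplemented with positive and negative predictive values, precision, recall". External validation in CPRD-AURUM then follows. No calibration target is given, and calibration is not linked to the success rule.

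Predicting accuracy is not defined. The section on identifying and quantifying predictors treats accuracy and AUC as two things, planning "curves of both AUC and prediction accuracy plotted against the number of risk factors". The Introduction compares two existing models by AUC, 0.827 against 0.725. It also describes what prediction models in general could do for screening: "discriminating patients into risk categories, from which investigation intensity could be planned".

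**The concern.** A model that outputs absolute probabilities has to rank patients correctly and also put the risk at the right level. Risk curves over time depend on the level, and so do any categories set by predicted risk. The stated rule tests only a gain in accuracy. The protocol's own comparison of existing models suggests AUC as the natural reading, and on that reading the rule tests ranking only.

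A model could then meet the definition of success while its absolute risks are too high or too low in CPRD-AURUM. There is some reason to check: derivation uses Vision practices and Read codes, while validation uses EMIS Web practices in England and SNOMED CT. Defining the metric as AUC would not close the gap, so this point remains even if the undefined term is clarified that way.

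**Working it through.** **Inputs from the document.** Mean risk 1.7% (Sample size). AUC 0.827 for the better of the two existing models (Introduction). The required gain of 5% (Ethics and dissemination). The 1.7% is a prevalence, but the Sample size section uses it as an event risk: 0.017 × 377 996 = 6425.9, against the stated 6425. It is used the same way here. The document gives no calibration figure to reproduce.

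**Assumptions, not from the document.** Logistic-normal risks; observed/expected ratios of 0.5 and 2.0; a 5% risk cut for illustration; a calibration slope of 0.7 for one further case.

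**Step 1: risk distribution.** Let logit(p) = a + b·z, with z standard normal. Solving for mean(p) = 0.017 and AUC = 0.827 by numerical integration gives a = −4.92 and b = 1.37.

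**Step 2: shift the level and keep the ranks.** Observed outcomes follow p. Predictions are q, with logit(q) = logit(p) + s, and s is chosen so that mean(q) = 0.017 / (observed/expected).

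- Observed/expected 0.5: mean(q) = 0.034, s = 0.77.
- Observed/expected 2.0: mean(q) = 0.0085, s = −0.73.

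Adding a constant does not change the order of patients, so AUC is 0.827 in every case.

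**Step 3: share at or above 5%.** The share is 1 − Φ((logit(0.05) − a − s)/b), with logit(0.05) = −2.944.

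| Observed/expected | Standardised cut | Share at or above 5% | AUC |
|---|---|---|---|
| 1.0 | (−2.944 + 4.924)/1.370 = 1.445 | 7.4% | 0.827 |
| 0.5 | (−2.944 + 4.924 − 0.766)/1.370 = 0.886 | 18.8% | 0.827 |
| 2.0 | (−2.944 + 4.924 + 0.734)/1.370 = 1.981 | 2.4% | 0.827 |

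**Step 4: wrong spread instead of wrong level.** Divide the linear predictor by 0.7 and re-centre it so that the mean stays at 1.7%. The top 1% are then given a mean risk of 38.0% against a true 22.7%. AUC is again unchanged.

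**Step 5: a model that just meets the rule.** A 5% relative gain on 0.827 is 0.827 × 1.05 = 0.868. In a simulation of 1,000,000 patients at that AUC, halving, keeping or doubling every risk gave AUC 0.868 each time. The expected/observed ratios were 0.51, 1.01 and 2.01.

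**Step 6: other readings of accuracy, same model as Step 1.**

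- Brier score: 0.0158 when calibrated and 0.0166 at observed/expected 0.5, so it responds. The no-information value is 0.017 × 0.983 = 0.0167.
- Correct classification at a 5% cut: 92.3% when calibrated, 81.7% at observed/expected 0.5, 96.7% at 2.0. It penalises over-prediction and rewards under-prediction.
- Correct classification at a 0.5 cut: 98.3% with true risks and 98.3% with every risk cut to a tenth, so it is nearly blind. Calling nobody AF already scores 98.3%. The largest relative gain over that is 0.017/0.983 = 1.7%, so a 5% gain over it is out of reach.

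**The case against.** **Calibration is planned.** It is listed for all models, and the report is to follow TRIPOD, so a large error in AURUM should be visible to readers. This stands. The gap is only that calibration does not enter the success definition.

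**Release is not automatic.** A reader might infer that the rule by itself decides release and clinical use. The text does not support that. Release and the general-practice tool are both worded as possibilities, and the same paragraph calls for impact research and commits to device regulation.

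**Not every reading is blind.** A reader might also infer that no version of accuracy could detect miscalibration. Step 6 shows otherwise: a Brier-type score responds, and so does classification at a 5% cut, although the latter improves under under-prediction and is no safeguard. The point is confined to AUC, the c-statistic and other rank-based readings.

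**Ranking may be enough for some uses.** Inviting a top-ranked fraction for screening needs discrimination only, and the protocol fixes no risk threshold. The sentence on risk categories is general background. This is fair, but the planned probabilities by horizon still depend on the level of risk.

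**Limits belong in a fuller document.** Numerical limits could well sit in a full protocol or analysis plan, and their absence here is not the finding. The article does, however, state a complete definition of success, and that definition names accuracy alone.

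**Conclusion.** The concern holds in this limited form. The protocol's only success rule is a gain in accuracy, and on a rank-based reading it cannot detect miscalibration of the absolute risks the model is meant to produce. In the worked example AUC stays at 0.827 while the share at or above 5% risk goes from 7.4% to 18.8% or 2.4%.

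These figures rest on a logistic-normal risk distribution, a prevalence used as event risk, an illustrative cut and assumed observed/expected ratios. They show what the rule would let through. Nothing in the protocol indicates that a twofold error in AURUM is likely, and a reader should not infer that one is expected. The change is worth making because the definition can label a miscalibrated model a success and the measure needed to prevent that is already planned.

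**What to change.** Extend the success definition in Ethics and dissemination. Success should require the stated gain and also acceptable calibration in CPRD-AURUM, with the observed/expected ratio and the calibration slope inside limits that the investigators set before validation. State the horizon or horizons at which this is judged.

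If only calibration fails, report the discrimination gain but do not call the model a success until it has been recalibrated and rechecked. The recheck should use data not used for the recalibration.

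The cost is small in text and adds little analysis, since calibration metrics are already planned. Success becomes somewhat harder to claim, and limits must be chosen and defended; the protocol offers no figure for them. Recalibrating within AURUM, if it comes to that, would use up part of the external validation sample.
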